#### Secondary outcome

3.10.2

Days of vomiting, gastric retention (measured by aspirating with a 5‐mL syringe before each feeding) and abdominal distension (defined as a 24‐h abdominal circumference increase of ≥1.5 cm).Weight gain (kg), change of length and head circumference during hospitalization.Length of hospital stay (day).Change of abdomen circumference, gastric retention volume and frequency of defecation (comparison between day 1 and day 7).

Disappearing of vomiting, abdominal distention gastric retention and the amount of milk increased day by day are seemed as alleviation of FI (Lu & Lan, 2020).

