## BACKGROUND

1

Over 14.9 million babies are born prematurely across the world every year, and the number is still increasing (Heinonen et al., 2016). Due to immature gastrointestinal function, premature newborns especially those born before 34 weeks, are susceptible to feeding intolerance (FI) (Asadi et al., 2019), and its morbidity could achieve 70% (Ng et al., 2019). Currently, there is no universal definition of FI, the widely accepted one is the following: the gastric residual volume (GRV) was 50% greater than the last feeding volume, with abdominal distension or vomiting (Moore & Wilson, 2011).

FI could badly influence newborns' health. During the neonatal period, it may lead to malnutrition, delayed enteral nutrition, prolonged hospitalization, growth restriction and increase the risk of sepsis and serious gastrointestinal complications such as necrotizing enterocolitis (NEC) (Meister et al., 2019; Neu, 2007). Additionally, it may lead to long‐term negative outcomes such as visceral obesity, glucose intolerance, and increased risk of cardiovascular disease, negative neurodevelopmental outcomes in adulthood (Asadi et al., 2019). At present, treatment for FI includes breastfeeding, modifications in feeding regimes, use of probiotics or medicine, but effectiveness and safety of these methods remain controversial (Basu & Smith, 2020; Fanaro, 2012; Sukwuttichai et al., 2021), feeding intolerance (FI) is still a thorny issue affecting the prognosis of preterm infants. So it is important to find an effective way to cure FI, contributing to recovery of gastrointestinal function and improving long‐term health of preterm infants.

In recent years, massage therapy has been frequently used in neonatal wards for the prevention of FI. Studies have shown that massage could prevent gastric retention and abdominal distention in premature infants, and reduce the length of stay. In addition, massage could stimulate the digestive system and the vagus nerve in premature infants, potentially improving their physical growth (Diego et al., 2007; Heinonen et al., 2016; Tekgündüz et al., 2014). However, there is no consensus on the efficacy of massage in the treatment of FI.

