### Participants: Inclusion/exclusion criteria

3.3

Table 1 specifies the criteria for inclusion, exclusion, termination and exit criteria. Inclusion and exclusion criteria were defined according to previous literature (Baldassarre et al., 2019; Ng et al., 2018; Yakobson et al., 2020).

**TABLE 1 nop21733-tbl-0001:** Inclusion, exclusion, termination and exit criteria.

*Inclusion criteria*
Meet the FI diagnostic criteria
Admitted to the Neonatal Treatment Center of the Affiliated Children's Hospital of Chongqing Medical University within 24 h after birth
28 weeks ≤ gestational age ≤ 34 weeks, 1000 g ≤ birth weight ≤ 2000 g
In clinically stable condition
The neonate's guardians are willing to participate in this trial
*Exclusion criteria*
Apgar score less than 4 at 5 min
Neonates with skin disease, intestinal obstruction, sepsis, necrotizing enterocolitis, gastrointestinal malformation, congenital heart disease, central nervous system disorder, immune deficiency, or any other disease that may affect the ability to eat and normal growth before recruitment
Neonates who need surgery which requires general anaesthesia (except for ligation of patent ductus arteriosus) before the day of randomization
Neonates whose blood pressure is not stable (using dopamine <5 mg /kg/min is permitted)
Ventilator dependent or FiO_2_ (Fraction of inspired oxygen) > 40% on the day of randomization (continuous positive airway pressure, nasal intubation, oxygen mask are allowed)
Neonates who are diagnosed with Grade III or IV ventricular haemorrhage (IVH) on the day or before randomization
*Termination criteria*
Discharge in a stable condition with doctor's advice
*Exit criteria*
Death or discharge before achieving total enteral nutrition
Guardian request to withdraw from the trail

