### Data collection and management

3.11

Table 3 shows the schedule of evaluations. Data of each participant were collected on case report forms (CRFs) and then electronically recorded on a computer. CRF1 records participants' baseline information and it was filled in when neonates were included in the trial. CFR2, which includes information about the outcome of this trial, will be filled in during the trial and when neonates discharge with advice.

**TABLE 3 nop21733-tbl-0003:** Schedule of evaluations.

	Staff member	CRF	T1	T2	T3	T4	T5	T6
Symptom of FI	Neonatal assistant	CRF1	**×**					
Informed consent	Research assistant	CRF1	**×**					
Contact information	Research assistant	CRF1	**×**					
Sex	Neonatal physician	CRF1		**×**				
Gestational age	Neonatal physician	CRF1		**×**	**×**			
Mode of delivery	Neonatal physician	CRF1		**×**				
Apgar score	Neonatal physician	CRF1		**×**				
Maternal issues	Neonatal physician	CRF1		**×**				
Weight	Neonatal nurse	CRF2		**×**	**×**			**×**
Gastric residual volume	Neonatal nurse	CRF2				**×**	**×**	
Abdominal circumference	Neonatal nurse	CRF2				**×**	**×**	
Frequency of defecation	Neonatal physician	CRF2				**×**	**×**	
Length	Neonatal nurse	CRF2		**×**				**×**
Head circumference	Neonatal nurse	CRF2		**×**				**×**
Time to achieving total enteral nutrition	Neonatal physician	CRF2						**×**
Duration of abdominal distension	Neonatal physician	CRF2						**×**
Duration of vomiting	Neonatal physician	CRF2						**×**

*Note*: T1, screening; T2, baseline evaluation; T3 randomization; T4, day 1 of intervention; T5, day 7 of intervention; T6, discharge.

Once recorded, data are locked to prevent changes. Access to the data is limited to researchers directly involved with this trial. Data about participants who discontinue or deviate from intervention will not be included in statistical analysis.

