## DISCUSSION

4

This article describes the methodology of a study designed on the effects of massage on the treatment of preterm FI. A total of 104 preterm infants will be included in this trial, they will be stratified according to their birth weight and then assigned to the massage group or control group randomly. Variables include index on FI and physical development will be recorded.

We combined abdominal massage and skin stroking in our trail. According to scientific literature, abdominal massage stimulates gastrointestinal peristalsis by increasing vagus nerve activity (Moyer et al., 2004). Additionally, it can affect abdominal pressure and have a mechanical and reactive impact on the intestines (Harrington & Haskvitz, 2006; Liu et al., 2005). Skin stroking may activate the baroreceptors and mechanoreceptors of the skin as well as the vagal efferent fibres that innervate the digestive system (Diego et al., 2005; Field, 2016). Consequently, we hypothesized that a combination of abdominal massage and skin stroking may be more effective than earlier interventions.

There were several studies investigating the benefits of massage, but low sample size and differences in the duration and frequency of massage in these studies were their limitations (Ghasemi et al., 2019; Shaeri et al., 2017; Soheila et al., 2013; Zaky Mohamed & Saied Ahmed, 2018). This study with accurate methodology, longer interventions and large sample size has the potential to give proof that preterm infant massage benefits in the recovery of gastrointestinal function and promotes growth and development if it is conducted successfully. Owing to the lack of research on the treatment of FI, it is anticipated that this study will fill a large gap in the literature.

Massage also has other advantages for preterm infants, such as promoting physical development, strengthening the immune system, reducing stress, and reducing the time of hospitalization (Niemi, 2017). So, this study may give a novel nursing practice for enhancing the long‐term outcomes of premature infants and could be widely used in neonatal wards.

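### Total growth to discharge mixes growth rate with length of stay, so a shorter stay biases the growth comparison against massage and could dilute, hide or reverse a benefit

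*Protocol article*

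**What the plan says.** Section 3.10.2 of the protocol article lists "Weight gain (kg), change of length and head circumference during hospitalization" among the secondary outcomes. The unit for weight is kilograms, and the window is the whole stay. The next item in the same list is "Length of hospital stay (day)".

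Table 3 (section 3.11) fits this reading. Weight is marked at T2, T3 and T6; length and head circumference are marked at T2 and T6. The table note reads "T4, day 1 of intervention; T5, day 7 of intervention; T6, discharge", so every growth window closes at discharge and no growth measurement is marked at day 7. Table 1 ties discharge to clinical stability and medical advice ("Discharge in a stable condition with" is how the entry begins), without a fixed day or weight.

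On direction, the Background says of earlier massage studies that they prevented gastric symptoms "and reduce the length of stay". The Discussion lists among the advantages of massage "reducing stress, and reducing the time of hospitalization", and hopes to show that it "promotes growth and development".

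Section 3.12 compares continuous outcomes between two groups by t-test, or by Wilcoxon–Mann–Whitney test if they are not normal. Its only adjustment is a logistic regression for unnamed confounders.

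**The concern.** A change measured up to discharge depends on how fast the infant grows and on how long the infant is observed. Here the observation time is a post-randomisation outcome that the treatment is expected to reduce. Randomisation does not balance it, and an unadjusted comparison of totals attributes any difference in time to growth.

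The article expects two benefits, faster growth and earlier discharge, and on this measure they pull in opposite directions. The trial could then report no growth benefit, or an apparent deficit, when daily growth was equal or better with massage.

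The article avoids the problem elsewhere. Abdominal circumference, gastric retention volume and defecation frequency have a fixed window ("comparison between day 1 and day 7"); growth does not.

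**Working it through.** The article states no figure for the growth outcomes, so there is none to reproduce. It also gives no expected stay, reduction in stay or growth rate. Everything below that uses such a value is an assumption, shown over a range.

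**Inputs**
- Days by which stay is shortened, s: assumed 2.6 to 7. The middle value, 5.2, is the difference in time to full enteral nutrition in section 3.4 (33.5 − 28.3 = 5.2 days). It is borrowed for scale and is not a stay figure.
- Growth rate, v: assumed 15 to 25 g/day.
- Control-arm stay, L: assumed 30 to 50 days.
- Proportional rise in growth rate with massage, r: varied.

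**Step 1: equal growth rates (r = 0).** Total gain is v × stay, so the massage arm gains v × s less.
- s = 2.6, v = 15: 39 g
- s = 5.2, v = 15, 20, 25: 78, 104, 130 g
- s = 7, v = 25: 175 g

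The range is 39–175 g with identical daily growth.

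**Step 2: relative size.** The relative change in total gain is (1 + r)(L − s)/L − 1. The rise in growth rate at which the arms show no difference is r = L/(L − s) − 1. For s = 5.2 days:

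| L (days) | Change in total gain if r = 0 | Break-even r |
|---|---|---|
| 30 | 24.8/30 − 1 = −17.3% | 30/24.8 − 1 = 21.0% |
| 40 | 34.8/40 − 1 = −13.0% | 40/34.8 − 1 = 14.9% |
| 50 | 44.8/50 − 1 = −10.4% | 50/44.8 − 1 = 11.6% |

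Over the full grid, the loss at r = 0 runs from 5.2% (L = 50, s = 2.6) to 23.3% (L = 30, s = 7). The break-even runs from 5.5% to 30.4%.

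**Step 3: the sign.** At L = 40 and s = 5.2 the change in total gain is 0.87(1 + r) − 1:
- r = 0: −13.0%
- r = 10%: −4.3%
- r = 20%: +4.4%
- r = 30%: +13.1%

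Below break-even a true benefit appears as a deficit. Above it the benefit still shows but is smaller than it should be: a 20% faster rate appears as 4.4%.

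**Step 4: does the stated analysis correct this?** The t-test and the rank test compare the totals as they stand. Logistic regression is for a binary outcome and does not fit a continuous gain. Section 3.12 names neither a rate nor an allowance for stay.

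**The case against.** A reader might infer that an effective massage is bound to look as if it reduced growth, or that the two benefits cancel. The documents do not support either. Step 3 shows that the sign depends on whether the rise in growth rate exceeds break-even, and exact cancellation happens only at that value.

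A reader might also take 5.2 days as the trial's expected reduction in stay. It is not: section 3.4 gives it for time to full enteral nutrition, and the article gives only a direction for stay.

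Discharge in practice may wait for a target weight. Table 1 states no such rule, but if one applied, total weight gain would be pushed towards equality between the arms. That would not produce false harm, though the measure would still say little about growth.

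The consequence is also limited. Growth is one of several secondary outcomes, and length of stay is reported beside it, so a careful reader could see the two together. An analysis plan that is not shown might add a derived rate. This does not remove the point, because the article does not leave the measure open: it fixes the unit and the window, and that definition is what is at fault.

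Finally, velocity to discharge still ends at an event that treatment may bring forward. If growth is slow during intolerance and faster afterwards, average velocity over unequal windows keeps some dependence on stay. That objection stands, and the fix allows for it.

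**Conclusion.** The point holds as a bias in a stated definition. Total weight, length and head-circumference gain to discharge mixes growth rate with length of stay, and a shorter stay biases the unadjusted comparison against massage. The result could be a diluted, hidden or reversed growth benefit; which of these is not determined by the documents.

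The 39–175 g range is an illustration. It rests on an assumed 15–25 g/day, equal in both arms, and an assumed 2.6–7 day reduction in stay. It also assumes that discharge does not wait for a target weight and that growth is roughly constant over the stay. The primary outcome and the sample size are not affected.

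**What to change.** Define the growth outcomes as velocity: weight in g/kg/day from randomisation (T3) to discharge (T6), and length and head circumference in cm/week from baseline (T2) to discharge. T2 is the only measurement of length and head circumference before discharge in Table 3. Compare the arms with adjustment for the starting value and the birth-weight stratum. Keep total gain as a descriptive result, shown beside length of stay, and note when interpreting velocity that it still depends somewhat on the window if growth is not constant.

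The cost is a change of wording before analysis. The measurements are already scheduled. Table 3 has no row for discharge date, but day of recruitment is in Table 2 and length of stay is an outcome, so the intervals should be obtainable; the sponsor should confirm that the T2, T3 and T6 dates are recorded. No new visit and no change to the sample size is needed. Section 3.14 says recruitment was unfinished when the article was submitted, and section 3.12 places the analysis after all data are collected, so at that time the definition could still be changed before analysis.

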### Statistical analysis

3.12

After the data for the entire sample has been collected, it will be performed using SPSS 25.0 software package. Missing data will be forecasted and filled using multiple imputations. A logistic regression model will be used to adjust for multiple potential confounders plain. Measurement data obeying the normal distribution will be expressed as mean (standard deviation), and t‐test will be used for comparing between two groups. Non‐normally distributed variables will be expressed as median (interquartile range), and compared by the use of non‐parametric Wilcoxon–Mann–Whitney test. Classification data will be described as cases count (construct Proportional) and compared using the chi‐square test or non‐parametric Wilcoxon–Mann–Whitney test. The confidence interval will be set at 95%. *p* < 0.05 will be considered statistically significant.

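### Day 1 to day 7 changes in three secondary outcomes are compared without using the day-1 value as a covariate, which costs precision, and the plan does not place that reading before the first massage

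*Protocol article*

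**What the plan says.** Section 3.10.2 (Secondary outcome) includes "Change of abdomen circumference, gastric retention volume and frequency of defecation (comparison between day 1 and day 7".

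Table 3 in section 3.11 schedules gastric residual volume, abdominal circumference and defecation frequency at T4 and T5 only. The table note reads "T3 randomization; T4, day 1 of intervention; T5, day 7 of intervention; T6, discharge". None of the three is scheduled at T2 (baseline evaluation), although weight, length and head circumference are.

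Section 3.12 (Statistical analysis) says that for normally distributed measurements a "t‐test will be used for comparing between two groups", and that other measurements are "compared by the use of non‐parametric Wilcoxon–Mann–Whitney test". The only adjusted model is this: "A logistic regression model will be used to adjust for multiple potential confounders". Neither its outcome nor its covariates are named.

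The Abstract describes these three measurements as taken both ahead of and following the seven-day intervention. Section 3.8 gives massage twice daily from the first intervention day.

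**The concern.** Each infant will have a day-1 and a day-7 value, but the named tests use the first only by subtraction. Subtraction fixes the coefficient on the day-1 value at one. The best coefficient is usually below one, so the raw change carries avoidable noise. If one arm happens to start with larger residuals, part of that difference passes into the estimated effect. Allocation is stratified by birth weight alone, so nothing in the design balances day-1 severity. At the planned size this could blur a real effect on the outcomes closest to the proposed mechanism.

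The time of the day-1 reading matters as well. It falls after randomization, on a day when one arm is massaged, and the article does not say whether it comes before the first session. A defecation count for that day could span massage sessions in one arm only. If the reading is affected by treatment, both the change score and an adjustment for it could remove part of the effect.

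**Working it through.** **The plan's own figures.** No sample size or power is given for these outcomes. Section 3.4 gives 41 per arm for the primary outcome. That number cannot be reproduced because no standard deviation is printed. The loss step does reproduce: 41/(1 − 0.2) = 51.25, rounded up to 52 per arm, 104 in total. I use 41 per arm only as the evaluable size.

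**Inputs.**
- n = 41 per arm (section 3.4).
- Significance level 0.05 (section 3.12), taken as two-sided because the article does not say.
- Correlation ρ between day 1 and day 7: not given, assumed 0.3 to 0.9.
- True effect: not given, assumed 0.5 SD of the day-7 value.
- Equal SDs on the two days: assumed first, then relaxed.

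**Precision with equal SDs.** Per infant, in units of SD²:
- raw change: 2(1 − ρ)
- day-7 value adjusted for day 1 (ANCOVA): 1 − ρ²
- ratio, adjusted to raw: (1 + ρ)/2

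Power is Φ(0.5/√(2v/41) − 1.96), with v the variance above.

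| ρ | v, change | v, adjusted | Ratio | 41 per arm by change is worth, with adjustment | Power, change | Power, adjusted |
|---|---|---|---|---|---|---|
| 0.3 | 1.40 | 0.91 | 0.65 | about 27 | 48% | 66% |
| 0.5 | 1.00 | 0.75 | 0.75 | about 31 | 62% | 74% |
| 0.7 | 0.60 | 0.51 | 0.85 | about 35 | 83% | 89% |
| 0.9 | 0.20 | 0.19 | 0.95 | about 39 | above 99% | above 99% |

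The day-7 value alone (v = 1) has 62% power. Below ρ = 0.5 the raw change is therefore less precise than ignoring day 1 altogether.

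**Unequal SDs.** Let k be the day-1 SD divided by the day-7 SD. The ratio becomes (1 − ρ²)/(1 + k² − 2ρk). At ρ = 0.5:
- k = 0.5: 0.75/0.75 = 1.00
- k = 0.7: 0.75/0.79 = 0.95
- k = 1.5: 0.75/1.75 = 0.43

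The gain can be nil or much larger. In large samples the ratio does not exceed 1.

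**Chance imbalance.** The standard error of the day-1 difference between arms is √(2/41) = 0.22 SD. With equal SDs, an observed day-1 difference D shifts the expected change-score estimate for that allocation by (1 − ρ)D in size. For D = 0.22 SD the shift is about 0.15, 0.11 and 0.07 SD at ρ = 0.3, 0.5 and 0.7. Averaged over allocations, D is zero and so is the shift.

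**The case against.** The strongest reply is that the article condenses a fuller plan. Section 3.12 lists tests by data type and sets no model for each outcome, and covariates for secondary outcomes commonly belong in an analysis plan that is not shown. A change outcome is also compatible with adjustment, since regressing the change on group and day-1 value gives the same treatment effect as modelling day 7. This limits the certainty but does not remove the point, because the article states which tests will be used. Its one adjusted model, logistic regression, suits a binary outcome and not these variables.

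A reader might infer that the comparison is biased, because infants are selected with extreme values that drift back toward the average. The documents do not support that. Randomization applies the same selection to both arms, so regression to the mean cancels on average. The selection argument is also uneven. The Background's definition rests on a large residual together with distension or vomiting, which fits gastric residual volume. Distension is later defined as a rise in circumference over 24 hours, not as an extreme absolute value. Defecation frequency is not in the definition at all. Nor is it certain that the arm with the worse start will look more improved. That is a tendency, which vanishes in the k = 0.5, ρ = 0.5 case above.

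Two further objections stand. The variance ratios apply to linear analysis and do not carry over directly to rank tests or stool counts, so they should not be read as extra infants for every outcome. The adjustment also depends on a reading time that the article does not state.

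**Conclusion.** The point holds as one of efficiency and robustness. The stated analysis is valid on average but uses the day-1 value poorly. With equal SDs, adjustment lowers the variance by 35%, 25%, 15% or 5% at ρ = 0.3, 0.5, 0.7 or 0.9. Both ρ and equal SDs are assumptions, and other SD ratios can erase or enlarge the gain.

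The timing problem is real in a limited sense. The Abstract implies a reading before intervention, while Table 3 puts the first one on an intervention day after randomization. A reader might conclude that the day-1 values are contaminated by treatment. The article does not show that; it only fails to exclude it.

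The primary outcome and the sample size are untouched.

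**What to change.** 1. Name the analysis for the three outcomes: the day-7 value (or, equivalently, the change) in a linear model with group, day-1 value and birth-weight stratum. For skewed residual volumes use a log scale or a rank-based version. For defecation use a count model with the day-1 count as covariate.
2. Reconcile the Abstract with Table 3 by stating that the day-1 residual and circumference are read before the first massage, and that the defecation count covers a stated window ending before it. Apply the same clock rule in both arms.
3. For infants already enrolled, report whether the day-1 readings preceded massage, and adjust only for pre-massage values. Where that cannot be shown for an outcome, the day-7 value adjusted for stratum alone avoids conditioning on a treated reading.

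The cost is small: revised analysis wording, a stated reading time, some extra analysis and a check of existing records. No added visits are needed. Recruitment began in April 2021 and was still open at submission (section 3.14), so the model can be fixed before unblinding, but reading times cannot be corrected for infants already treated.
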